## Follow-up Visit (Day 7)

A subsequent visit will be scheduled after 5-9 days of product dosing (target Day 7). Every attempt will be made to schedule appointment after 7 days of dosing to ensure adequate exposure. If a participant has discolored or malodorous vaginal discharge or suspected cervicitis at any Study Visit, an appropriate clinical and laboratory work-up will be conducted (see Appendix IV). If a participant has a genital ulcer, tests will be conducted for syphilis or herpes simplex as appropriate. Continuation in the study will be based on the severity of the abnormality noted as described in Appendix IV.

## Clinical Procedures

- Update locator information.
- Review interim sexual history, medical history, AE information, and concomitant medication information.
- Review daily study records, note the time of last application of the product, and conduct adherence review.
- Count and record the number of used and unused tubes and dispose of used tubes in accordance with the guidelines.
- Collect blood to measure serum progesterone, estradiol and tenofovir levels.
- Perform speculum exam including
- Visual inspection of vagina and cervix,
- pH sample from vaginal wall,
- Swab for wet prep and PSA-specific membrane test, and
- CVL collection.
- If abnormalities are noted, refer to Appendix IV for procedures to be followed.
- Schedule Study Visit for Day 14 and complete all required data collection forms.
- Review applicator instructions, remind participant to abstain from sexual intercourse and remind participant to continue bedtime dosing.

## Laboratory Procedures

- Record vaginal pH measurement.
- Examine wet mount by direct microscopy to detect *T. vaginalis*, *C. albicans* infections, clue cells for BV, and/or sperm. Perform whiff test and record results.
- Conduct PSA-specific membrane test for semen.
- Measure serum progesterone, estradiol and tenofovir levels.
- Process, spin, aliquot and freeze CVL supernatant for cytokines.
- Stain cell pellets with monoclonal antibodies against leukocyte phenotypic antigens for CD45 (hematopoietic cells), CD19 (B cells), CD3, CD4, CD8 (T cells), CD14 (macrophages) and CD11 (dendritic cells) and analyze by seven-color FACS.
- Measure IgG, IgA, IL-1, IL-1, IL-2, IL-6, IL-8, IL-10, IL-12, IFN-, IFN-, TNF-, MIP-1, MIP-1, RANTES, SLPI, TGF-, IL-1ra.
- Measure HNP1-3, HD-5, HD-6, hBD-1, hBD-2, hBD-3 and lactoferrin.
- Measure total protein concentration in CVL (BCA, Pierce).
- Evaluate anti-viral and anti-bacterial activity.
- Measure tenofovir level in CVL supernatant and cell pellet.

## Follow-up Visit (Day 14)

A subsequent visit will be scheduled after 12-15 days of product dosing (target Day 14). Every attempt will be made to schedule appointment after 14 days of dosing to ensure adequate exposure. If a participant has discolored or malodorous vaginal discharge or suspected cervicitis at any Study Visit, an appropriate clinical and laboratory work-up will be conducted (see Appendix IV). If a participant has a genital ulcer, tests will be conducted for syphilis or herpes simplex as appropriate. Continuation in the study will be based on the severity of the abnormality noted as described in Appendix IV.

## Clinical Procedures

- Update locator information.
- Review interim sexual history, medical history, AE information, and concomitant medication information.
- Review daily study records, note the time of last application of the product, and conduct adherence review.
- Count and record the number of used and unused tubes and dispose of used and/or remaining tubes in accordance with the guidelines.
- Collect blood to measure serum progesterone, estradiol and tenofovir levels.
- Perform speculum exam including
  - Visual inspection of vagina and cervix,
  - pH sample from vaginal wall,
  - Swab for wet prep and PSA-specific membrane test,
  - CVL collection
- If abnormalities are noted, refer to Appendix IV for procedures to be followed.
- Schedule Final Visit 3-8 days later.
- Complete all required data collection forms.
- Remind participant to abstain from sexual intercourse.

## Laboratory Procedures

- Record vaginal pH measurement.
- Examine wet mount by direct microscopy to detect *T. vaginalis*, *C. albicans* infections, clue cells for BV, and/or sperm. Perform whiff test.
- Conduct PSA-specific membrane test for semen.
- Measure serum progesterone, estradiol and tenofovir levels.
- Process, spin, aliquot and freeze CVL supernatant for cytokines.
- Stain cell pellets with monoclonal antibodies against leukocyte phenotypic antigens for CD45 (hematopoietic cells), CD19 (B cells), CD3, CD4, CD8 (T cells), CD14 (macrophages) and CD11 (dendritic cells) and analyze by seven-color FACS.
- Measure IgG, IgA, IL-1, IL-1, IL-2, IL-6, IL-8, IL-10, IL-12, IFN-, IFN-, TNF-, MIP-1, MIP-1, RANTES, SLPI, TGF-, IL-1ra.
- Measure HNP1-3, HD-5, HD-6, hBD-1, hBD-2, hBD-3 and lactoferrin.
- Measure total protein concentration in CVL (BCA, Pierce).
- Evaluate anti-viral and anti-bacterial activity.
- Measure tenofovir level in CVL supernatant and cell pellet.

## Final Visit (Day 21)

## A final visit will be scheduled after 16-21 days of product dosing (Target Day 21). This visit will mark the end of the subject’s participation in the study.

**Clinical Procedures**

- Update locator information.
- Review interim sexual history, medical history, AE information, and concomitant medication information.
- Review daily study records.
- Collect blood to measure serum tenofovir levels.
- Perform speculum exam including
  - Visual inspection of vagina and cervix,
  - pH sample from vaginal wall,
  - Swab for wet prep and PSA-specific membrane test, and
  - CVL collection.
- If abnormalities are noted, refer to Appendix IV for procedures to be followed.
- Complete all required data collection forms.
- Complete Termination Form.

## Laboratory Procedures

- Record vaginal pH measurement.
- Examine wet mount by direct microscopy to detect *T. vaginalis*, *C. albicans* infections, clue cells for BV, and/or sperm. Perform whiff test.
- Conduct PSA-specific membrane test for semen.
- Measure serum tenofovir levels.
- Process, spin, aliquot and freeze CVL supernatant for cytokines.
- Stain cell pellets with monoclonal antibodies against leukocyte phenotypic antigens for CD45 (hematopoietic cells), CD19 (B cells), CD3, CD4, CD8 (T cells), CD14 (macrophages) and CD11 (dendritic cells) and analyze by seven-color FACS.
- Measure IgG, IgA, IL-1, IL-1, IL-2, IL-6, IL-8, IL-10, IL-12, IFN-, IFN-, TNF-, MIP-1, MIP-1, RANTES, SLPI, TGF-, IL-1ra.
- Measure HNP1-3, HD-5, HD-6, hBD-1, hBD-2, hBD-3 and lactoferrin.
- Measure total protein concentration in CVL (BCA, Pierce).
- Evaluate anti-viral and anti-bacterial activity.
- Measure tenofovir level in CVL supernatant and cell pellet.
- Serum and CVL samples will be batched and stored for measurement of tenofovir and immune mediator determinations.

## 7.2 Interim Contacts and Visits (ad hoc)

Interim contacts and visits may be performed at participant request at any time during the study. All interim contacts and visits will be documented in participants' study records and on applicable case report forms.

Some interim visits may occur for administrative reasons (for example, the participant may have questions for study staff). Interim visits may also occur in response to AEs experienced by study participants.

When interim contacts or visits are completed in response to participant reports of AEs, study clinicians will assess the reported event clinically and provide or refer the participant for appropriate medical care.

**7.3 Specimen Preparation, Handling and Shipping**

Unused drug will be shipped to Gilead Sciences, Inc. and samples for measurement of tenofovir levels will be shipped in accordance with IATA specimen shipping regulations.

**7.4 Biohazard Containment**

## Appropriate blood and secretion precautions will be employed by all personnel in the drawing of blood and shipping and handling of all specimens for this study, as currently recommended by the U.S. Centers for Disease Control and Prevention (CDC). Universal precautions will be observed at all times.

**8.0 ASSESSMENT OF SAFETY**

**8.1 Adverse Events**

All AEs, except vulvovaginitis and cervicitis will be graded using the Division of AIDS Table for Grading the Severity of Adult and Pediatric Adverse Events (DAIDS AE Grading Table), Version 1.0, December 2004. Vulvovaginitis and cervicitis will be graded as detailed in Appendix V. Study staff will document on case report forms all AEs reported by or observed in enrolled study participants regardless of severity and presumed relationship to study product. All AE reports should contain the date the AE occurred, a brief description of the event, the time of onset, the duration of the event, the severity, the treatment required (if any), the relationship to study drug, the study drug action taken, the outcome, and whether or not the AE is Serious. The investigator or designee will assess the relationship of all AEs to the study product based on the Manual for Expedited Reporting of Adverse Events to DAIDS, dated May 6, 2004, the Investigator’s Brochure, and his/her clinical judgment.

The expedited adverse event (EAE) reporting requirements and definitions for this study and the methods for expedited reporting of adverse events (AEs) to the DAIDS Regulatory Compliance Center (RCC) Safety Office are defined in “The Manual for Expedited Reporting of Adverse Events to DAIDS” (DAIDS EAE Manual, Final 1.0), dated May 6, 2004.  The DAIDS EAE Manual is available on the RCC website: http://rcc.tech-res-intl.com/eae.htm. The RCC Safety Office e-mail address is [[contact]](mailto:[contact]). The telephone number is [name] or [contact] and the fax number is [name] or [contact].

AEs reported on an expedited basis will be documented on the DAIDS Expedited Adverse Event Reporting Form (EAE Reporting Form) available on the RCC website: http://rcc.tech-res-intl.com/eae.htm.

This study uses the Intensive Level of expedited AE reporting as defined in the DAIDS EAE Manual. The study agent that must be considered in determining relationships of AEs requiring expedited reporting to DAIDS are 1% tenofovir gel/placebo, and the study agent delivery applicators.

The Division of AIDS Table for Grading the Severity of Adult and Pediatric Adverse Events (DAIDS AE Grading Table), Version 1.0, December 2004 will be used and is available on the RCC website at [http://rcc.tech-res-intl.com](http://rcc.tech-res-intl.com/)/eae.htm. Additional grading parameters are found in Appendix V: Severity Grading for Vulvovaginitis and Cervicitis.

AEs will be reported on an expedited basis at the Intensive Level during the Protocol-defined EAE Reporting Period, which is the entire study duration for an individual subject (from study enrollment until study completion or discontinuation of the subject from study participation for any reason).

After the end of the Protocol-defined EAE Reporting Period stated above, the study team will report serious, unexpected, clinical suspected adverse drug reactions if the team becomes aware of the event on a passive basis, i.e., from publicly available information.

**8.2 Local regulatory requirements**

Information on all AEs experienced by study participants will be included in reports to the FDA and other applicable government and regulatory authorities. Study staff will report information on AEs to the MMC/AECOM IRB and GCRC in accordance with all applicable regulations and site-specific requirements.

As required by New York State law, all positive results for chlamydia, gonorrhea, HIV and syphilis will be reported to the New York City and State Departments of Health.

**8.3 Social harms reporting**

Participants may become embarrassed, worried, or anxious when completing their HIV risk assessment and/or receiving HIV counseling. They also may become worried or anxious while waiting for their HIV test results. Trained counselors will be available to help participants deal with these feelings.

Although the study site will make every effort to protect participant privacy and confidentiality, it is possible that participants' involvement in the study could become known to others, and that social harms may result (i.e., because participants could become labeled as HIV-infected or at "high risk" for HIV infection). For example, participants could be treated unfairly or discriminated against, or could have problems being accepted by their families and/or communities.

Women in abusive relationships may be unable to avoid sexual activity due to risk of physical harm. The study team will carefully inquire whether participants are able to decline intercourse and will not enroll any subjects who are evasive or uncertain in their responses.

## 9.0 CLINICAL MANAGEMENT

**9.1 Toxicity Management**

In response to AEs reported by study participants and/or observed upon exam by study staff, the study site investigator or designee will recommend either continuation or holding gel use consistent with the criteria in Appendix IV. Product use also will be held or discontinued in the event of a expedited adverse event (EAE) that is judged by the site Investigator or designee to be definitely, probably, possibly, or probably not related to the study gel or applicator.

**9.2 Other Disease Events**

Study staff will comply with all applicable local requirements to report communicable diseases including HIV and other reportable STI identified among study participants and their partners (if obligated by local law) to local health authorities. Participants will be made aware of all reporting requirements during the study informed consent process. As required by New York State law, all positive results for chlamydia, gonorrhea, HIV and syphilis will be reported to the New York City and State Departments of Health.

**9.3 Pregnancy**

If a participant is found to be pregnant at the screening or enrollment visits, she will discuss the results with the clinician and will not continue in the study. She will be referred for care by the study clinicians. If she becomes pregnant during the course of the study, she will discontinue study product and be referred for care. The study team will attempt to obtain pregnancy outcome data on any women who become pregnant while on study drug.

## 9.4 Breastfeeding

Currently, it is unknown if there are any effects of tenofovir gel on breast-milk. Though it is unlikely that the gel will pass through breast milk, systemic absorption of the gel into the blood may affect breast milk and cause harm to an infant. Therefore, participants must agree to abstain from breastfeeding throughout the course of their participation in the study.

**9.5 Criteria for Discontinuation**

Accrual into this study will be suspended if two or more participants experience similar grade 3 or higher AEs (as defined by the DAIDS Table for Grading the Severity of Adult and Pediatric Adverse Events, Version 1.0, December 2004) judged possibly, probably, or definitely related to product use. The protocol team in collaboration with the Safety Committee and NIH NIAID/DAIDS Medical Officer then will review all pertinent data and determine whether to continue accrual and product use. The team may decide to stop the study at this time, or at any such time that the team agrees that an unacceptable type and/or frequency of AEs have been observed.

The study may be discontinued at any time by the IRB, the NIH, the pharmaceutical supporters or designees, the FDA or other government agencies as part of their duties to ensure that research subjects are protected.

Monitoring of AEs/EAEs will be ongoing through regular reviews (safety monitoring). If needed, the protocol team will convene ad hoc meetings in the event of an abnormal number of reported AEs/EAEs judged definitely, probably, possibly, or probably not related to study gel or applicator, or any other conditions deemed as an emergency event by team members.

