**10.6 Safety Review**

The PI is responsible for continuous close monitoring of all AEs that occur among study participants. For this study, accrual will be suspended if two or more study participants experience similar grade 3 or higher AEs (as defined by the DAIDS Table for Grading Severity of Adverse Experiences) judged possibly, probably, or definitely related to product use. The protocol team, in collaboration with the Safety Committee and NIH NIAID/DAIDS Medical Officer, will review all pertinent data and determine whether to continue accrual and product use. A decision to stop the study may be made by the team at this time, or at any such time that the team agrees that an unacceptable type and/or frequency of AEs has been observed.

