**13.5 Study Discontinuation**

Once a participant has enrolled in the study, the study site will make every reasonable effort to retain her for the complete study period. Given the relatively small study sample size, and the importance of ascertaining all outcomes among study participants, 100 percent retention of enrolled participants is targeted.

However, participants may withdraw from the study for any reason at any time. The Principal Investigator (PI) also may withdraw participants from the study in order to protect their safety and/or if they are unwilling or unable to comply with required study procedures.

During the study, participants with any abnormal condition will be treated according to standard clinical practice. A participant with a clinical toxicity outcome (see Appendix IV) who is discontinued from further product use will be considered to have reached a study endpoint. Participants also may be withdrawn if the study sponsor or regulatory authorities terminate the study prior to its planned end date.

Every reasonable effort will be made to complete a final evaluation of participants who terminate from the study prior to completion, and study staff will record the reason(s) for all withdrawals from the study in participants’ study records.

If at the screening or enrollment visits, a participant is found to have an abnormality on pelvic exam or a urinary tract infection, she will be ineligible to enroll in the study. Following treatment for candida vaginitis, bacterial vaginosis or urinary tract infection, she may be eligible to be re-screened for participation in the study. A minimum interval of one month is required between treatment and re-screening and all exclusion criteria will apply. If a participant is found to be pregnant, she will be referred for care.

Accrual into this study will be suspended if two or more participants experience similar grade 3 or higher AEs (as defined by the DAIDS Table for Grading Severity of Adverse Experiences) judged possibly, probably, or definitely related to product use. The protocol team in collaboration with the Safety Committee and NIH Medical Officer then will review all pertinent data and determine whether to continue accrual and product use. The team may decide to stop the study at this time, or at any such time that the team agrees that an unacceptable type and/or frequency of AEs have been observed.

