## Appendix V: Severity Grading for Vulvovaginitis and Cervicitis

|  | Vulvovaginitis | Cervicitis |
| --- | --- | --- |
| Grade 1 | Vulvar and vaginal discomfort (including itching or burning), pelvic exam findings indicative of inflammation, and/or other exam findings (including findings involving epithelial disruption) that do not require medical therapy and that cause no or minimal interference with usual social and functional activities | Cervical inflammation or other findings on exam (including erythema, mucopurulent discharge, and/or friability) that do not require medical therapy and that cause no or minimal interference with usual social and functional activities |
| Grade 2 | Vulvar and/or vaginal discomfort (including itching or burning), pelvic exam findings indicative of inflammation, and/or other exam findings (including findings involving epithelial disruption) that require minimal medical therapy (such as a course of topical or oral antibiotics or antifungals) or cause greater than minimal interference with usual social and functional activities | Cervical inflammation or other findings on exam (including erythema, mucopurulent discharge, and/or friability) that require minimal medical therapy (such as a course of oral antibiotics) or that cause greater than minimal interference with usual social and functional activities |
| Grade 3 | Vulvar and/or vaginal discomfort (including itching or burning), pelvic exam findings indicative of inflammation, and/or other exam findings (including findings involving epithelial disruption) that result in inability to perform usual social and functional activities and/or require significant medical intervention such as a surgical procedure or hospitalization | Cervical inflammation or other findings on exam (including erythema, mucopurulent discharge, and/or friability) that require significant medical intervention (such as intravenous antibiotics) or that cause inability to perform usual social and functional activities |
| Grade 4 | Life threatening – vulvovaginitis with perforation | Life threatening |

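### As worded, the accrual-suspension rule does not count grade 3–4 vulvovaginitis or cervicitis, because those are graded by Appendix V and the rule cites only the DAIDS table

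*Protocol*

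**What the plan says.** Protocol section 8.1 sets up two grading scales. The general rule is: "All AEs, except vulvovaginitis and cervicitis will be graded using the Division of AIDS Table" (Version 1.0, December 2004). The two exceptions have their own scale: "Vulvovaginitis and cervicitis will be graded as detailed in Appendix V". Later in the same section, after the expedited-reporting rules, the protocol returns to the DAIDS table and adds: "Additional grading parameters are found in Appendix V: Severity Grading for Vulvovaginitis and Cervicitis".

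Appendix V runs from grade 1 to grade 4 for each condition. Grade 3 vulvovaginitis covers symptoms or findings "that result in inability to perform usual social and functional activities and/or require significant medical intervention such as a surgical procedure or hospitalization". Grade 3 cervicitis covers findings "that require significant medical intervention (such as intravenous antibiotics) or that cause inability to perform usual social and functional activities". Grade 4 is life-threatening disease in both columns.

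The suspension rule is stated three times:

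- Section 9.5: accrual stops if "two or more participants experience similar grade 3 or higher AEs (as defined by the DAIDS Table for Grading the Severity of Adult"; the table cited is Version 1.0 of December 2004, and the events must be judged at least possibly related to product.
- Section 10.6: the same trigger, for "similar grade 3 or higher AEs (as defined by the DAIDS Table for Grading Severity of Adverse Experiences").
- Section 13.5: the same again, for "grade 3 or higher AEs (as defined by the DAIDS Table for Grading Severity of Adverse Experiences) judged possibly, probably, or definitely related".

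None of the three mentions Appendix V.

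**The concern.** The rule defines its severity threshold by a table from which section 8.1 has expressly removed two conditions. An event that carries only an Appendix V grade has no DAIDS-table grade to compare with the threshold. Followed to the letter, any number of similar, related grade 3 or 4 cases of vulvovaginitis or cervicitis leaves the trigger untouched.

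The conditions left out are not marginal. The product is a vaginal gel, and the Appendix V vulvovaginitis scale takes in epithelial disruption as well as inflammation and discomfort. According to section 2.4, 77% of the AEs in the earlier Phase I study were confined to the genitourinary tract, and the one product termination it describes was for vulvar ulceration. The suspension rule is also the only study-level safety action in the protocol that follows automatically from a count of events. Its wording should give the result the authors intended for the organ most at risk.

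**Working it through.** **Text comparison.** The protocol gives no figure to reproduce here, so the main check is on wording.

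| Step | Source | Result |
|---|---|---|
| Scale for vulvovaginitis and cervicitis | 8.1, Appendix V | Appendix V, not the DAIDS table |
| Are grades 3 and 4 possible on that scale? | Appendix V | Yes, for both conditions |
| Scale that defines the trigger | 9.5, 10.6, 13.5 | A DAIDS table in all three |
| Is Appendix V named in the trigger? | 9.5, 10.6, 13.5 | No, in none |

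The literal gap follows directly.

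**How often could it matter?** The protocol gives no expected rate for these events, so rates have to be assumed. The only guide is the earlier Phase I study.

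- Completers: 60 HIV-uninfected + 24 HIV-infected = 84 (section 2.3).
- Severe AEs: four, of which the only one thought possibly related was lower abdominal cramping (section 2.4). The probably related genital event that ended product use was moderate.
- Taking severe to mean grade 3 or higher, there were 0 related severe cases of vulvovaginitis or cervicitis in 84 women.

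One-sided 95% upper bound for 0 of 84:

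1 − 0.05^(1/84) = 0.0350, or 3.5%.

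The chance that at least two of n women have such an event, each with independent probability p, is

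P(X ≥ 2) = 1 − (1 − p)^n − n·p·(1 − p)^(n−1).

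For example, with n = 12 and p = 0.01: 1 − 0.8864 − 0.1074 = 0.0062.

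| Assumed rate p | n = 12 (active gel only) | n = 24 (placebo gel at the same rate) |
|---|---|---|
| 1% | 0.6% | 2.4% |
| 2% | 2.3% | 8.3% |
| 3.5% (upper bound) | 6.4% | 20.5% |

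These are chances that two or more events occur, not that the wording changes a decision. They pool vulvovaginitis with cervicitis, whereas the rule requires similar events, and they include second events that fall after accrual has closed. At a given rate they are therefore upper limits on how often the trigger should have fired.

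**The case against.** The strongest reply is that the exclusion is inferred and never stated. Section 8.1 describes Appendix V as adding to the DAIDS grading parameters, both scales run from 1 to 4, and sections 10.6 and 13.5 cite the table by a looser title with no version. All this suggests that the parenthesis names the grading scheme in general and was not meant as a carve-out. On that view a sensible team would count these events. As a reading of intent this stands. It does not repair the wording: 8.1 makes an explicit exception for the two conditions, and the sentence about additional parameters is not carried into the rule.

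One could also argue that an event recorded under Appendix V might still be tested against the DAIDS table for the purpose of the trigger. The exception in 8.1 speaks against that.

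The second reply is that other safeguards remain:

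- the team meets weekly, and serious AEs are reported within 24 hours (10.5);
- product is held or discontinued for related expedited events (9.1);
- the team can meet ad hoc over an abnormal number of AEs and can stop the study at any time (9.5);
- Appendix IV stops product in the individual for vaginitis, ulceration or generalized erythema, although under suspected cervicitis product provisionally continues.

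These are real and are why the risk is low, but none of them pauses accrual automatically. The ad hoc meeting and the stop depend on judgement, and the holds act on one woman at a time. Scheduled Safety Committee review is at least every 3 months; at even accrual of 24 women over 12 months, about 24 × 3/12 = 6 could enrol between reviews. Serious-event reporting may also miss some cases, since Appendix V grade 3 can be met by inability to carry on usual activities alone. That last point is an inference, because the protocol does not define a serious event.

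**Conclusion.** The concern holds. As written, the rule in 9.5, 10.6 and 13.5 leaves out grade 3–4 vulvovaginitis and cervicitis. It is a drafting gap and almost certainly not a deliberate exclusion, and it does not mean these events go unmonitored.

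The size is small. The chance of two or more qualifying events ranges from under 1% to about 6% if only the active arm is at risk, and up to about 20% at the upper bound if both gels carry the same rate. These figures assume that severe in the earlier study means grade 3 or higher, that completers are the right denominator, and that its rate carries over. That study mixed 0.3% and 1% gel, once and twice daily use, and HIV-infected and uninfected women, so they are a rough guide only. The textual finding does not depend on them.

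The wording should still be corrected: it is a stated safety rule that gives an unintended result for the target organ.

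**What to change.** In sections 9.5, 10.6 and 13.5, define the trigger as grade 3 or higher by the DAIDS AE Grading Table, Version 1.0, December 2004, or by Appendix V for vulvovaginitis and cervicitis. Leave the threshold as it is: two or more participants with similar, related events. Using the same table title and version in all three places is an editorial tidy-up to make at the same time.

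The cost is one phrase in three sections. The only downside is a possible additional accrual pause, for events that the team and Safety Committee would want to review in any case.
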